**Methods:**

In this prospective randomized trial 70 patients with KOA will be recruited using a diagnostic block of four genicular nerves. Two groups will be created through software randomization: a CRFA group (35 patients) and a CRYO group (35 patients). The target of the interventions will be four genicular nerves; the superior medial, superior lateral, inferior medial, as well as the medial (retinacular) genicular branch from vastus intermedius. The primary outcome of this clinical trial will be the efficacy of CRFA or CRYO at 2-, 4-, 12-and 24-weeks post-intervention using the Numerical Rating Pain Scale (NRPS). The secondary outcomes are the safety of the two techniques, as well as the clinical evaluation using the Knee Injury and Osteoarthritis Outcome Score (KOOS), the Oxford Knee Score (OKS), and the 7-point scale of Patient Global Impression of Change (PGIC).

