Cryoneurolysis involves the application of cold temperatures (− 20 to − 100 °C) to a peripheral nerve, leading to Wallerian degeneration and subsequent analgesia, while the nerve retains its ability to regenerate [12–16]. In contrast to CRFA which completely ablate the targeted nerve, CRYO has the ability to disrupt nerve function while structural elements of the nerve bundle remain intact. This allows for complete regeneration and functional recovery of the nerve over time. CRYO studies, so far, are primarily targeting the infrapatellar branch of the saphenous nerve (IPBSN), a sensory nerve that innervates the anterior and inferior parts of the knee capsule and/or the anterior femoral cutaneous nerve (AFCN) [13, 14, 16]. The CRYO probe that will be used in this study (IceSphere 1.5 CX, Galil Medical Ltd) creates also a spherical lesion of ice around the tip thus increasing the likelihood of degenerate the targeted nerves.

Clinical evidence in general, suggests that both CRFA and CRYO are safe and effective procedures for the symptomatic management of KOA pain [11–18].

The primary objective of our proposed trial is to evaluate the efficacy of CRFA or CRYO at 2-, 4-, 12- and 24-weeks post-intervention in patients with painful KOA using the Numerical Rating Pain Scale (NRPS).

The secondary objectives are the comparison of safety and tolerability of the two interventions, as well as the patient’s clinical outcome at 12- and 24-weeks post-intervention, using the Knee Injury and Osteoarthritis Outcome Score (KOOS) and the Oxford Knee Score (OKS). Also, the 7-point scale of Patient Global Impression of Change (PGIC) will be used at 2-, 4-, 12-, and 24-weeks post-intervention to capture the patients’ feelings of improvement.

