Patients will discontinue all pain medications (opioids, NSAIDS, anti-depressants and anti-convulsant drugs), supplements, chondroprotective drugs, and other alternative therapies for KOA for 10 days prior to the screening/baseline visit. During follow-up, patients will be prohibited from undergoing any other adjunctive treatment for KOA, including steroid injections, viscosupplementation, and pain medications. Serious local complications from either CRFA or CRYO and the need for medications for pain relief will be a criterion for study discontinuity.

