### Outcomes

Patients will be assessed at baseline and 2-, 4-, 12-, and 24-weeks post-intervention (Table 1).

**Table 1 Tab1:** Timeline of the study

Timepoint	Enrollment		Allocation		Assessment times		
	− 3 w	− 1 w	0 w	2w	4 w	12 w	24 w
Enrollment							
Eligibility screening	√						
Informed consent	√						
Genicular nerve block		√					
Allocation			√				
Outcome measures							
NPRS (primary)			√	v	√	√	√
KOOS			√	–	v	√	√
OKS			√	–	v	√	√
PGIC			–	–	v	√	√
Complications medications			Intra-op				
			√	v	√	√	√
			√	v	√	√	√

*NPRS* Numerical Pain Rating Scale, *KOOS* Knee Injury and Osteoarthritis Outcome Score, *OKS* Oxford Knee Scores, *PGIC* Knee Patient Global Impression of Change

The primary outcome would be the efficacy of CRFA or CRYO at 2-, 4-, 12- and 24-weeks using the Numerical Rating Pain Scale (NRPS). The secondary outcomes will be the potential improvement of the KOOS, and OKS at 12- and 24-weeks post-intervention. Patients will be also asked about their impression of improvement using the 7-point scale of Patient Global Impression of Change (PGIC) [34]; PGIC responders are the patients who indicate that they are either “very much improved” or “much improved” at each follow-up assessment. Expected side effects and complications (for example, bruising, swelling, numbness, inflammation, and/or erythema) involving percutaneous access to the nerves and the use of local anesthesia will be assessed at each follow-up visit and documented independently, except for loss of motor function outside the treatment area. The details of the timeline, assessments, and follow-up evaluations are presented in Table 1.

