### Implementation and blinding

Enrolment of participants will be performed by the main investigators ([name], [name]) at the outpatient office of our department according to the eligibility criteria listed above. The allocation sequence will be created by an investigator not involved in patient care (([name]), and the assignment of participants to interventions by a coordinator nurse at the radiological department who will be responsible for arranging the sessions. The primary investigators ([name], [name], [name]) will be blinded to the intended treatment until the time of intervention; CRFA or CRYO will be applied to each patient after the opening of the sealed opaqued envelope inside the interventional radiological department. Clinical evaluation at 15 days (NPRS, PGIC), 4 weeks (NPRS, PGIC), 12 weeks (NPRS, PGIC, OKS, KOOS), and 24 weeks (NPRS, PGIC, OKS, KOOS) will be performed by an orthopedic resident ([name]) not involved in the initial patient evaluation who will also be blinded to the applied intervention. Data analysists ([name]) and outcome adjudicators will be also blinded during the implementation of the data. Unblinding will be performed in case of severe adverse effects (intense pain, hematoma, nerve damage etc.).

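### The follow-up safety definition is narrower than the objective of comparing the safety of the two ablation techniques, and does not match the protocol's other safety passages

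*Protocol article*

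**What the plan says.** The Introduction sets the objective: "The secondary objectives are the comparison of safety and tolerability of the two interventions". The abstract agrees: "The secondary outcomes are the safety of the two techniques", followed by the clinical scores.

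The Outcomes section is where safety is put into operation. Its sentence on the secondary outcomes names two scores and not safety: "The secondary outcomes will be the potential improvement of the KOOS, and OKS at 12- and 24-weeks post-intervention". The safety content comes a little later, in one sentence. It opens with "Expected side effects and complications (for example, bruising, swelling, numbness, inflammation, and/or erythema", gives their source and timing as "involving percutaneous access to the nerves and the use of local anesthesia will be assessed at each follow-up visit", and ends "documented independently, except for loss of motor function outside the treatment area". Table 1, in the same section, has an entry for complications that starts intra-operatively and runs through the 2-, 4-, 12- and 24-week visits. That entry carries no limit on cause or expectedness.

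Other sections use wider language:
- The paragraph closing the CRYO technique section makes "Serious local complications from either CRFA or CRYO" a criterion for discontinuation.
- Implementation and blinding states: "Unblinding will be performed in case of severe adverse effects (intense pain, hematoma, nerve damage etc".
- Interim and additional analyses allows stopping for serious complications, with CRYO singled out as little tested.
- The Discussion says that complication rates will be recorded.

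**The concern.** The Outcomes sentence narrows the safety outcome twice. The event has to be expected, and it has to be connected with needle access or local anaesthesia. Neither limit appears in the objective, which compares two techniques.

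The second limit matters more. The Strengths and limitations section places the contrast between the arms in the mechanism: heat damage that may be permanent, against freezing with Wallerian degeneration. A safety outcome tied to access and anaesthesia looks mainly at what the arms have in common and leaves unclear whether effects of the differing step belong to it. The same section contemplates a conclusion that CRYO is the safer technique. That conclusion needs a compared outcome that clearly contains the harms of each ablation. If staff applied the sentence as written, the recorded comparison would be incomplete where a difference is most plausible.

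**Working it through.** The protocol states no figure on this point, so the check sets the passages side by side.

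**1. Scope of the compared outcome**

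| Place | Events covered | Limit on cause | Use |
|---|---|---|---|
| Abstract; Introduction | Safety (and, in the Introduction, tolerability) of the two techniques | None | Secondary outcome or objective, between arms |
| Outcomes, safety sentence | Expected effects, with open-ended examples | Access and local anaesthesia | Assessed at each follow-up visit |
| Outcomes, Table 1 | Complications | None | Schedule, intra-operative to 24 weeks |
| End of CRYO technique | Serious local complications | Either technique | Discontinuation |
| Implementation and blinding | Severe effects, including nerve damage | None | Unblinding |
| Interim and additional analyses | Serious complications | None | Stopping |
| Discussion | Complication rates | None | Reporting intention |

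Only the second row says what kinds of event are assessed at follow-up, and it is the narrowest. The rows on discontinuation, unblinding and stopping are triggers for action and reach only serious or severe events. They do not place those events in the between-arm comparison. Table 1 gives timing, not content.

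**2. What the arms share**

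Both technique sections give 2–3 ml of 1% lidocaine at each target site under fluoroscopy, and the target nerves are the same. The overlap is not complete. The CRFA section adds a 17-gauge introducer, 1 ml of 2% lidocaine through it, and motor testing at 2 Hz. The CRYO section describes no counterpart. Access and anaesthesia are therefore largely common, and even the literal definition could show some difference between arms.

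**3. What falls outside on a literal reading**

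Two classes fall outside: unexpected events of any cause, and events attributed to heating or freezing. Numbness and inflammation are among the listed examples and could come from either source, so their status is unclear. The closing exception for motor loss can be read in more than one way, and the point does not rest on it.

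**4. What can be quantified**

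No harm rate is given for either arm. Any calculated bias would need assumed rates for access events and ablation events and an assumed share of the latter left out, and the answer would follow from those assumptions. One bound is useful as context. With 35 patients per arm and no recorded events, the one-sided 95% upper limit on a harm rate is 1 − 0.05^(1/35) = 8.2%. It has that meaning only for a harm that was within the scope of collection. It does not measure bias.

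**The case against.** The strongest reply is that the sentence is loosely written rather than restrictive. Its examples are open-ended, and several could follow ablation as readily as needle entry. No step is described in which an event is judged for cause and then discarded. Follow-up is assigned to a resident who is meant to be blinded to the intervention, so nothing suggests that numbness at 12 weeks would be rejected as an ablation effect. Table 1 has no cause limit, and the Outcomes text refers to it for the assessments. Serious harms of either technique are plainly recognised elsewhere.

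Most of this stands, and it rules out three stronger readings that a reader might infer. The first is that ablation-specific harms will never be counted: the documents do not say so, and Table 1 and the Discussion point the other way. The second is that the recorded safety difference is forced to zero: that would need identical access and anaesthesia and complete exclusion of ablation harms, and the documents support neither. The third is that interim stopping for serious complications is disabled: that section does not refer to the Outcomes wording.

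What the reply does not remove is the mismatch. Where the schedule, the triggers and the definition disagree, the person filling in the form has to choose. A condensed article may leave event coding, grading and reporting format to the full protocol or analysis plan, and their absence is not criticised here. A scope that is stated and too narrow is a different matter.

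**Conclusion.** The point holds as an inconsistency between the safety objective and the definition meant to serve it. The Outcomes sentence is narrower than the objective and conflicts with Table 1 and with the passages on discontinuation, unblinding, interim stopping and complication rates. Taken literally, it leaves unexpected events and harms of heating or freezing outside the compared outcome, although the ablation is the main difference between the arms.

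No size can be given, because there are no harm rates and no evidence of how the sentence is applied in practice. The conclusion rests on two readings: that this sentence is the only text here defining the content of follow-up safety assessment, and that its phrase about access and anaesthesia limits the events it covers. If the case forms already collect all complications regardless of cause, the defect is confined to the wording.

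**What to change.** Reword the Outcomes sentence so that the compared safety outcome is all adverse events, expected or unexpected, arising from any step of the procedure including the ablation. State that they are collected in the same way in both arms at the visits in Table 1 and compared between arms. List safety among the secondary outcomes in that section, as the abstract does. Then reconcile the abstract, the Introduction, the closing paragraph of CRYO technique, Implementation and blinding, Interim and additional analyses and the Discussion to that one definition. The elicitation checklist, grading and summary format can sit in the full protocol or analysis plan.

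The first patient was recruited on 31/8/2022, before the article appeared. If the forms have followed the narrow wording, the date of the change should be recorded, so that visits before and after it can be told apart in the analysis.

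The cost is small: a change of wording, a slightly longer complications form at visits already planned, and more minor events to record.

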### CRFA technique

Two to 3 ml of 1% lidocaine is used to anesthetize the skin and subcutaneous tissues before cannula insertion at each target site under fluoroscopic guidance. Thereafter, a 50–150 mm 17-gauge introducer needle will be placed to ablate the SLGN, SMGN, IMGN, and MRGN. One milliliter of 2% lidocaine will be injected through the introducer needles to anesthetize the area before ablation. After placement of the introducer needle, a 18 gauge, internally cooled 4-mm active tip RFA electrode (Coolief, Halyard Health, Alpharetta, GA, USA) will be placed into the introducer needle, and the positioning is checked again using fluoroscopy. The introducer is connected to COOLIEF* Cooled RF Advanced Generator that allows staggered start, stop and adjusting of 4 independent channels. Motor nerve activity will be excluded by testing at 2 Hz and 1 mA. The CRFA probes will be advanced, and ablation will be performed with lesion settings at 60 °C (80–90 °C adjacent tissue temperature) for 2.5 min. As mentioned before, this type of ablation creates a spherical lesion at the tip of the probe. Cooled RF electrodes include a thermocouple at the active electrode tip to provide a temperature-controlled lesion formation. This involves water-cooling of the active electrode tip during the duration of the process without tissue charring at the electrode tip; this mechanism doubles the lesion radius and increase the lesion volume by 5 times.

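### As worded, the complication-recording rule excepts loss of motor function outside the treatment area, and no other section says how that event is recorded

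*Protocol article*

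**What the plan says.** The recording rule is in the Outcomes section, below Table 1. Its subject is "Expected side effects and complications (for example, bruising, swelling, numbness, inflammation, and/or erythema"), tied to the percutaneous access and the local anaesthetic. These events "will be assessed at each follow-up visit and documented independently, except for loss of motor function outside the treatment area".

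Other places in the protocol article bear on the same event:

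- **Abstract, Methods:** "The secondary outcomes are the safety of the two techniques", together with the clinical scores.
- **Introduction:** "The secondary objectives are the comparison of safety and tolerability of the two interventions".
- **Table 1:** complications are marked intra-operatively and at 2, 4, 12 and 24 weeks. No exception is shown.
- **Implementation and blinding:** "Unblinding will be performed in case of severe adverse effects (intense pain, hematoma, nerve damage etc".
- **End of the CRYO technique section:** "Serious local complications from either CRFA or CRYO" are among the criteria for discontinuation.
- **Interim and additional analyses:** serious complications are a ground for stopping, with CRYO singled out as not yet thoroughly tested.

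**The concern.** A between-arm comparison of safety needs each relevant harm to be looked for in the same way, at the same visits, in both arms. The Outcomes sentence sets up such a rule and then excepts one event from it. Bruising and erythema would be recorded at every visit, while loss of motor function outside the treatment area need not be. Both treatments deliberately injure nerves, so motor loss belongs among the harms that a reader of the safety results will ask about.

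This is not a case of a condensed article leaving detail to a fuller document. The article makes an affirmative statement about what is excepted. Site staff who followed it would leave the event off the visit record unless something else prompted them to report it. The completeness of one line of the safety comparison, which is a stated secondary objective, is at stake.

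**Working it through.** No arithmetic applies. The point is which events must be recorded, and it does not depend on sample size, power or effect size. The check is to read the exception against every other statement on safety in the article and ask whether any of them puts the event back into the record.

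1. **Scope of the exception.** It covers loss of motor function outside the treatment area only. Motor loss inside that area is not excepted.

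2. **Table 1.** The table text is damaged in the copy at hand: the labels for complications and medications have run together. Both rows of marks beneath them are filled at 2, 4, 12 and 24 weeks, so complications are scheduled at every follow-up visit whichever row belongs to them. The table carries no exception and the sentence below it does. The two do not match.

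3. **Objective and outcome.** The Abstract and the Introduction make safety a secondary outcome and its comparison a secondary objective. Neither limits this to expected effects or to the treatment area. The stated comparison is therefore wider than the recording rule that feeds it.

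4. **Unblinding rule.** Implementation and blinding lists nerve damage among "severe adverse effects (intense pain, hematoma, nerve damage etc".) that lead to unblinding. This shows that the investigators regard nerve injury as a relevant harm. It is a trigger for action once an event is known; it does not require anyone to look for the event at each visit.

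5. **Discontinuation rule.** It is limited to complications that are both serious and local. It is not clear that a deficit outside the treatment area would count as local.

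6. **Interim rule.** It refers to serious complications without restriction, so a serious motor deficit could reach the interim review. It does not say how such events are ascertained, and it does not reach non-serious ones.

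**Result.** None of these places says how the excepted event is recorded. The rules in steps 4 to 6 can bring serious cases to notice. For non-serious or transient motor loss outside the treatment area, the only sentence that addresses its recording is the one that excepts it.

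**The case against.** The strongest reply is that the sentence is clumsy but harmless. Its subject is expected effects of needle access and local anaesthesia. On that reading, the exception says only that distant motor loss is not an expected effect of this kind and so falls outside the routine list, to be handled as an unexpected or serious event. The unblinding and interim rules presuppose that such events are detected, which fits this reading. Adverse-event definitions and forms are also commonly kept in the full protocol.

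Much of this stands. The benign reading is possible, and serious cases are not invisible. A reader might infer that the interim review loses a safety input, but this is not established, because the interim rule covers serious complications of any kind. What does not stand is the conclusion that nothing needs to change: the article neither states the benign reading nor describes the separate route, and a literal reader would leave the event off the visit record.

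A reader might also infer that the excepted risk differs between arms, because "Motor nerve activity will be excluded by testing at 2 Hz and 1 mA" appears for CRFA and no such step is described for CRYO. The documents do not support this. The test is made through the electrode and concerns motor fibres near it, whereas the exception concerns loss outside the treatment area.

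**Conclusion.** The point holds as a defect of wording with a real, limited consequence. Taken literally, the Outcomes sentence excepts one narrow event from per-visit assessment and documentation, no other section supplies a route for it, and the sentence conflicts with Table 1 and fits poorly with the safety objective and the listing of nerve damage as a severe adverse effect. Non-serious or transient cases could be missed in the between-arm safety comparison.

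The conclusion rests on a literal reading of the sentence and on the article alone; a full protocol that set out a separate reporting route would leave only the wording to correct.

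The size cannot be quantified. The article gives no rate for motor loss, and a confidence bound for zero events among the 35 patients in an arm would be the same for any event, before or after the correction, so it does not measure this defect. A reader might infer that the plan leaves motor harm as a whole out of the safety comparison. That goes too far: motor loss inside the treatment area is not excepted, and serious cases outside it may still surface. The primary pain outcome is unaffected.

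**What to change.** Delete the exception from the Outcomes sentence. Suggested wording: 'Loss of motor function, including outside the treatment area, is assessed and documented at every follow-up visit in both arms and is counted in the comparison of safety.'

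If the intent was that such loss is not an expected effect and is reported by another route, state that route, and say that it applies equally to both arms and feeds the safety comparison.

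In either case, reconcile the Outcomes sentence with Table 1, the secondary objective in the Introduction, the unblinding rule under Implementation and blinding, and the interim rule. The change concerns data collection only and leaves technique and clinical rules as they are. It costs one sentence in the protocol and one line on the existing visit form.
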